#### Clinical

The primary clinical outcomes are the proportion of residents prescribed vitamin D ≥800 IU/day at 6 and 12 months. The secondary prescribing outcomes are the proportion of residents prescribed ≥500 mg/day of elemental calcium and the proportion of high risk residents (*i.e.*, those with a fracture or documented osteoporosis) prescribed an osteoporosis medication (oral and IV bisphosphonates, teriparatide, denosumab) at 6 and 12 months. Other secondary outcomes include the number of falls, hip fracture and all fracture (hip, wrist, spine, foot, humerus, ribs, clavicle, ankle, other) for the data collection periods (*i.e.*, three months of falls and fracture data collected three times during the study, see Figure 1).

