3. DVD: At the first interactive educational session, the 10-minute ‘Meeting the Challenge of Osteoporosis and Fracture Prevention’ DVD is viewed, and a copy is left at the LTC home so that other staff and residents/families can be educated (available at http://www.osteoporosislongtermcare.ca[54]).

4. Performance reports (audit and feedback): Aggregate/facility-level data for vitamin D, calcium, and osteoporosis medication prescribing are presented in a graphical format at each interactive educational session. Reports are based on the previous month’s prescribing and are benchmarked against other ViD*OS* intervention homes. Confidential, individual performance reports are also provided to each physician.

5. Reminders/Point-of-care tools are distributed and discussed in the educational sessions. These tools include the process indicator checklist, treatment alert, and x-ray requisition stamp (summarized in Table 1). Tools were developed in consultation with the pharmacy provider, the *Ontario Osteoporosis Strategy in LTC*[54] steering group, and our pilot LTC home.

6. Action planning: This quality improvement component is built around the plan-do-study-act (PDSA) cycle [56,57]. In brief, the PDSA process engages teams in planning and managing change by breaking goals into manageable chunks, testing ideas and assessing the results in order to better monitor the impact of changes. Some LTC homes may be familiar with the PDSA process from the ‘Long-Term Care Best Practices Initiative’ [12]. After the learning module is presented, PAC teams discuss and complete an action plan work-sheet at sessions one and two to address barriers and identify organizational strategies, process changes, and specific action items for team members. Teams work on implementing action plans and progress is reviewed at the next session. Strategies generated from sessions are shared with other LTC homes.

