**Table 1 T1:** **Key Components of the Multifaceted ViD *****OS *****intervention**

Interactive Educational Sessions	Presentation of three learning modules that include a summary of best practices, special considerations for assessing/treating the elderly, key messages, integration of OP/fracture prevention into care processes, and a case study. Opportunity for discussion and active participation via problem-based learning and completion of action plans.
Expert Opinion Leader/ Study Coordinator	Expert opinion leader leads first and second interactive educational sessions via webinar (with study coordinator facilitating on-site). A Geriatric Nursing Consultant leads the third interactive educational session via webinar.
DVD	A 10-min DVD, ‘Meeting the Challenge of Osteoporosis and Fracture Prevention,’ is viewed at the first interactive educational session (and a copy left for the team to educate other/new staff members, residents, families). This DVD was created by the * Osteoporosis Strategy for LTC* (http://www.osteoporosislongtermcare.ca[54]) and is specific to the LTC context.
Performance Reports (Audit and Feedback)	Performance reports for vitamin D, calcium, and osteoporosis medications prescribing (aggregated for all residents in a home) and benchmarked against other ViD*OS* intervention homes, are presented at each interactive educational session. Confidential, individual performance reports are also provided to each physician.
Reminders/Point of Care Tools	Treatment Alert: A tool used by consultant pharmacists to alert physicians and nurse practitioners to assess and consider osteoporosis treatment for residents at increased risk for fracture (based on the 2010 Osteoporosis Canada Clinical Practice Guidelines [21].
	X-ray Requisition Stamp: A stamp labeled ‘please rule out vertebral fractures’ to add to chest X-ray requisitions.
	Process Indicator Checklist: This tool assists teams with creating internal processes and policies that support and sustain appropriate prescribing and other osteoporosis and fractures best practices (*e.g.*, admission/quarterly assessment, diagnoses documentation, ongoing staff education and training).
Action Planning for Quality Improvement	Discussion/completion of a work-sheet to set specific action items for team members, address barriers and facilitators, and outline best practices strategies. Homes work on action plans between study sessions.

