#### Control homes

Control homes will receive no intervention. After the intervention homes have completed the study, the control group will have the option of attending a group webinar that presents a summary of key messages from educational modules. They will also be provided with an opportunity to appoint an internal champion who will receive post-study resources and updates. All LTC homes (control and intervention) will also have the opportunity to access continuing education through professional meetings (*e.g.*, the Ontario Long-Term Care Association and the Ontario Long Term Care Physicians).

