#### LTC osteoporosis toolkit and website

Both control and intervention homes received the LTC Osteoporosis Toolkit in 2009/2010, which includes a 10-minute DVD, ‘Meeting the Challenge of Osteoporosis and Fracture Prevention,’ pocket cards, case studies, and posters. This toolkit was distributed to all Ontario LTC homes as part of the provincial government-funded *Ontario Osteoporosis Strategy*[59]. The toolkit was developed to increase awareness of best practices for osteoporosis and fracture prevention. An introductory group webinar was available to all LTC homes in Ontario to introduce the toolkit components. In late 2011, the *Ontario Osteoporosis Strategy for LTC* website (http://www.osteoporosislongtermcare.ca[54]) was launched and was promoted in all LTC homes across Ontario.

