#### Patient-level

Figure 2 provides an overview of the data collection time-line. De-identified clinical data including demographic, prescribing, and co-morbidities (from the Medication Administration Record) are collected from the pharmacy database by the Director of Systems Services at Medical Pharmacies ([name]).

Falls and fractures data for every resident are collected by a LTC staff member at each home for three-month periods at three times during the study (coinciding with prescribing data pulls, Figure 2). The information source used to populate the data collection spreadsheets may vary by LTC home and sources are documented by the study coordinator. With the recent wide-scale implementation of the RAI-2.0 assessments across Ontario LTC homes [34,35], future studies collecting information on falls and fracture data will likely use this as a data source. The RAI-2.0 is a standard assessment using common methodology and measures and is completed by trained assessors (typically within 14 days of admission and then on a quarterly basis).

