#### Blinding

Study participants, personnel, expert opinion leaders, and the analyst who provides the audit and feedback reports are not blinded to home allocation status. The outcome assessor ([name]) who downloads the demographic, prescribing, and co-morbidity data and the analyst who performs the final data analysis will be blinded to home allocation status. The staff members within each LTC home who are recording falls and fractures data are not blinded.

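### The all-fracture comparison, but not hip fracture, is open to differential detection because only intervention homes receive a prompt to look for spine fractures

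*Protocol article*

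**What the plan says.** - **Outcome.** The Clinical part of Study outcomes lists falls, hip fracture and a broader count as secondary outcomes. The broader count is "all fracture (hip, wrist, spine, foot, humerus, ribs, clavicle, ankle, other", so spine is a named component and hip also stands alone.
- **Comparison.** Quantitative analysis uses GEE to test for differences between groups, and fracture counts are among the outcomes listed. A between-arm comparison is therefore planned, although Aims and objectives speaks only of documenting falls and fractures.
- **Prompt.** Table 1 describes the "X-ray Requisition Stamp: A stamp labeled ‘please rule out vertebral fractures’ to add to chest X-ray requisitions". Multifaceted intervention components places it among the point-of-care tools given out at the educational sessions: "These tools include the process indicator checklist, treatment alert, and x-ray requisition stamp (summarized in Table 1".
- **Control arm.** The Control homes section says: "Control homes will receive no intervention". The LTC osteoporosis toolkit and website section says: "Both control and intervention homes received the LTC Osteoporosis Toolkit in 2009/2010". That toolkit is listed as a DVD, pocket cards, case studies and posters, with no stamp.
- **Recording.** Under Blinding: "The staff members within each LTC home who are recording falls and fractures data are not blinded". Under Patient-level data collection: "The information source used to populate the data collection spreadsheets may vary by LTC home".

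**The concern.** Many vertebral fractures come to light only when someone looks for them on a film. If one arm is prompted to look and the other is not, the recorded number of spine fractures can differ between arms even when the true number does not. Randomisation does not prevent this, because the difference arises after allocation and through the allocated treatment. GEE handles correlation within homes, and the planned covariates (age, gender, co-morbidities, number of medications) do not describe detection, so the model cannot remove it.

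The all-fracture ratio could then suggest an excess under a fracture-prevention programme, or hide part of a real reduction. The Discussion says the pilot is meant to supply effect sizes for later research, so a distorted ratio could be carried into the planning of a larger trial.

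**Working it through.** **1. Is there a figure in the plan to reproduce?** Not on this point. The article gives no fracture rate, spine share, frequency of chest films or power for fractures. Its only design calculation concerns vitamin D prescribing and has no bearing here.

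**2. Is the difference in detection tied to arm?** Reading the sections together:
- the stamp is an intervention tool (Multifaceted intervention components; Table 1);
- control homes receive no intervention, and the toolkit sent to all homes does not list the stamp;
- spine is inside the all-fracture count, which is compared between arms.

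So the stamp acts on the spine component in one arm only. It does not act on hip fracture, which is a separate outcome.

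**3. How large could it be?** Let
- R = true rate ratio, intervention to control, taken as the same for spine and other sites;
- s = share of spine among fractures recorded in control homes;
- k = spine-fracture detection in intervention homes relative to control homes.

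Per control fracture, the intervention arm records R × [(1 − s) + s × k], so

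apparent ratio = R × [1 + s × (k − 1)].

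Both s and k are assumptions.

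| True R | s | k = 1.5 | k = 2 | k = 3 |
|---|---|---|---|---|
| 1.0 | 0.05 | 1.025 | 1.05 | 1.10 |
| 1.0 | 0.10 | 1.05 | 1.10 | 1.20 |
| 1.0 | 0.20 | 1.10 | 1.20 | 1.40 |
| 0.8 | 0.05 | 0.82 | 0.84 | 0.88 |
| 0.8 | 0.10 | 0.84 | 0.88 | 0.96 |
| 0.8 | 0.20 | 0.88 | 0.96 | 1.12 |

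Examples: 1 × [1 + 0.20 × (3 − 1)] = 1.40, and 0.8 × [1 + 0.20 × (2 − 1)] = 0.96. In the second, most of a true 20% reduction disappears.

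**4. What does unblinded recording do?** Suppose intervention staff fail to record a fraction u of all fractures. The ratio becomes (1 − u) × R × [1 + s × (k − 1)]. With R = 1, s = 0.20 and k = 1.5:
- u = 0: 1.10
- u = 0.10: 0.90 × 1.10 = 0.99
- u = 0.20: 0.80 × 1.10 = 0.88

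More complete recording in intervention homes would push the other way. It is plausible too, since Table 1's process checklist, another intervention tool, encourages documentation of diagnoses. The stamp has a direction of its own; the sum of the two sources does not.

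**5. What if spine is left out?** Then s = 0 and the stamp term vanishes: apparent ratio = R. The factor (1 − u) remains.

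**The case against.** The strongest case on the other side has four parts.

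*The stamp may hardly act.* The tools are given out and discussed, and nothing requires their use. The text does not say at which session the stamp first goes out, so not every window need be affected. This stands as a limit on size. It does not alter the fact that the prompt goes to one arm.

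*Old or silent deformities may never be entered as events.* The objective concerns fractures during the study period, and rules for completing the spreadsheet may well sit in a fuller document. It would therefore be wrong to say that old fractures will be counted. But a new silent fracture is also found only if someone looks, so a rule against old fractures would reduce the problem without removing it.

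*A stronger reading is tempting.* A reader might infer that the whole fracture comparison is biased against the intervention. The documents do not support that. Hip fracture is untouched by the stamp, and unblinded recording can run either way. Information sources differ by home, but nothing ties them to arm, so with homes randomised they add noise and no systematic shift.

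A reader might also build a much larger ratio. Assume 2,400 intervention residents and 4 fractures per 100 resident-years: 2,400 × 0.25 × 0.04 = 24 events per window. Assume 5-10% have a film and 10-20% of films are positive: 2,400 × 0.05 × 0.10 = 12 to 2,400 × 0.10 × 0.20 = 48 extra events. The ratio is then 36/24 = 1.5 to 72/24 = 3.0. None of these rates is in the article. The sum also needs every film stamped, every finding entered as an event, and no such fracture found in control homes. It is a ceiling for its inputs, not an estimate.

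*The outcome matters little here.* This is a pilot centred on feasibility, fractures are secondary, and the article openly states that the recorders are unblinded. This stands and sets the weight of the point.

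**Conclusion.** The point holds for the all-fracture comparison only. Detection of one component of the outcome differs by arm through the intervention itself, and the analysis cannot correct this. Taken alone, the stamp tends to raise the all-fracture ratio. For a true ratio of 1, a spine share of 5-20% and 1.5- to 3-fold detection, the apparent ratio is about 1.03 to 1.40; every one of these inputs is assumed. Once unblinded recording is considered, the net direction is not fixed.

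Hip fracture is not touched by the stamp. The primary vitamin D outcome is unaffected, because it comes from pharmacy data downloaded by a blinded assessor. This is a minor matter on a secondary outcome of a pilot: a cheap improvement.

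**What to change.** Before the final analysis, specify two between-arm fracture comparisons: hip fracture, and non-vertebral fracture (the all-fracture list without spine). Report spine fractures descriptively by arm, with a note that intervention homes were given a prompt to look for them. Data monitoring says that no formal comparison of arms takes place until the end of the study, so this can be settled without knowledge of results.

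The cost is wording, provided that site is captured, as the outcome's list of sites suggests. Some true symptomatic spine fractures leave the comparison. Bias from unblinded recording remains in both comparisons and should be stated as a limitation of unknown direction.

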**Figure 1 F1:**
[figure not shown]
Overview of ViDOS Intervention.

#### Study design

The ViD*OS* study is a pilot, cluster RCT [41] comparing a multifaceted KT intervention with a control group. The intervention is delivered over a 12-month time period with data collection extending to 16 months. Allocation by clusters of LTC homes rather than individual practitioners was chosen to minimize contamination because we are targeting interdisciplinary care teams. Because few other studies have examined this type of interdisciplinary multifaceted intervention within LTC, the study was designed as a pilot RCT that emphasizes feasibility outcomes [42].

#### Randomization and consent

Stratified block randomization was used to randomly allocate LTC homes to the intervention or control arm of the study (recruitment is now closed). LTC homes were stratified based on home size and profit/non-profit. Profit status was taken into consideration because there is some evidence that the quality of care is higher in non-profit homes compared to for-profit homes [43-45]. The allocation sequence was computer generated using nQuery 6.0 software by an off-site research member who is not involved in the recruitment, enrollment of clusters, or data analysis. Once the appropriate representative from the home was consented, the independent member assigned intervention and control groups based on the sequence and notified the coordinating centre. Because the homes are not blinded to treatment arms, the homes were informed of their allocation.

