### Data analysis

#### Quantitative analysis

Data from the trial will be analyzed and reported in accordance with the CONSORT criteria [41,63,64]. The baseline characteristics will be reported as mean (standard deviation) or median (minimum, maximum) values for continuous variables and as counts (percent) for categorical variables. The primary feasibility outcomes will be analyzed using descriptive statistics expressed as percent and corresponding 95% confidence intervals (CI). Our primary analyses will be performed using the intention-to-treat principle. The generalized estimating equations (GEE) technique, assuming an exchangeable correlation structure [65], will be used to determine differences between groups for the proportion of residents prescribed vitamin D, calcium and other osteoporosis medication, and number of fractures or falls. The GEE method will take into account the clustered nature of the data, given that residents treated within a LTC home are expected to be similar or correlated (clustered variable will be the LTC home). For the model, the unit of analysis will be the resident and the unit of inference will be the home. There is an increased risk of imbalance at the resident-level because of the home-level randomization. Therefore, resident baseline characteristics that will be included in this analysis are: age, gender, co-morbidities, and the number of prescribed medications. Unadjusted and adjusted odds ratios (OR) and corresponding 95% CIs will be reported. All statistical analyses will be performed using the SAS/STAT 9.2 software package (SAS Institute Inc., Cary, NC, USA) with the criterion for statistical significance set at α ≤0.05.

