#### Sample size

Our sample size was calculated to detect a difference in the percentage of residents prescribed ≥800 IU/daily vitamin D at follow-up in the intervention versus control groups. We assumed an average of 120 residents per LTC home and that 30% of residents were prescribed ≥800 IU/daily vitamin D at baseline [33]. We postulate a 20% increase in vitamin D prescribing in the intervention group and a 5% increase in the control group (to account for the potential impact of other province-wide initiatives such as the *Ontario Osteoporosis Strategy for LTC*). Based on these assumptions, to detect a 15% difference in prescribing between the groups with an intracluster correlation of 0.10 (two-sided test with significance = 0.05), a sample size of 2,160 residents from 18 LTC homes in each of the intervention and control groups is required to achieve 82% power. Factoring in a potential 10% dropout rate, the recruitment target was 40 LTC homes (20 = intervention, 20 = control).

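### Homes are randomised within strata of size and profit status, but the covariates named for the between-arm GEE are all resident-level; adding the strata is a cheap gain in precision

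*Protocol article*

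**What the plan says.** The Randomization and consent section states that "LTC homes were stratified based on home size and profit/non-profit". It justifies the choice of profit status on the ground that "there is some evidence that the quality of care is higher in non-profit homes compared to for-profit homes". It gives no comparable reason for home size.

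The Quantitative analysis section names the method: "The generalized estimating equations (GEE) technique, assuming an exchangeable correlation structure", with the home as the clustering variable. After noting that randomising homes can leave residents imbalanced, it says that the "resident baseline characteristics that will be included in this analysis are: age, gender, co-morbidities, and the number of prescribed medications". It adds that "Unadjusted and adjusted odds ratios (OR) and corresponding 95% CIs will be reported". Home size and profit status are not named for any model. The Facility-level data collection section shows that bed numbers and profit status are recorded for each home.

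The Sample size section makes no allowance for stratification.

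**The concern.** Stratified allocation balances the arms on the stratifying factors, so differences between strata largely drop out of the arm comparison. A model that omits those factors does not know this. It counts differences between strata as ordinary home-to-home noise and attaches a standard error that is too large for the design. The interval is then wider than it needs to be, and the benefit of stratifying does not reach the reported result.

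The article itself suggests that profit status may be related to care. The natural expectation is therefore that the analysis follows the groups within which homes were randomised.

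**Working it through.** **Inputs from the Sample size section.** "We assumed an average of 120 residents per LTC home and that 30% of residents were prescribed" the target dose at baseline. "We postulate a 20% increase in vitamin D prescribing in the intervention group and a 5% increase in the control group". The calculation is "to detect a 15% difference in prescribing between the groups with an intracluster correlation of 0.10 (two-sided test with significance = 0.05". Read as absolute increases, the rates are 35% (control) and 50% (intervention), with 18 homes and 2,160 residents per arm and a stated power of 82%.

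**The plan's own figure.**
- Design effect: 1 + (120 − 1) × 0.10 = 12.9.
- Effective residents per arm: 2,160 / 12.9 = 167.4.
- Variance term: 0.35 × 0.65 + 0.50 × 0.50 = 0.4775.
- SE of the difference: √(0.4775 / 167.4) = 0.0534.
- Power: Φ(0.15 / 0.0534 − 1.96) = 80.2%.

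This is within two points of the stated 82%. I use 80.2% as the like-for-like baseline.

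**Effect of leaving the strata out.** Let R2 be the share of between-home variance that the strata explain. The article does not give it, so it is an assumption throughout. With stratified allocation the true design effect is 0.9 + 12 × (1 − R2), while the model without strata still estimates 12.9. The SE is therefore overstated by the factor √(12.9 / true design effect).

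- R2 = 0.10: 0.9 + 10.8 = 11.7; √(12.9 / 11.7) = 1.050; true SE 0.0534 / 1.050 = 0.0509.
- R2 = 0.20: 0.9 + 9.6 = 10.5; √(12.9 / 10.5) = 1.108; true SE 0.0534 / 1.108 = 0.0482.

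Power with strata omitted is Φ((0.15 − 1.96 × 0.0534) / true SE). With strata included it is Φ(0.15 / true SE − 1.96).

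| Assumed R2 | SE overstated by | Power, strata omitted | Power, strata included | Points given up |
|---|---|---|---|---|
| 0 | 0% | 80.2% | 80.2% | 0 |
| 0.10 | 5% | 81.4% | 83.9% | 2.5 |
| 0.20 | 11% | 82.7% | 87.6% | 4.9 |

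**Simulation, home-level analysis.** With 40 equal homes in four strata, 20 homes per arm and 4,000 runs, power without and with strata was 82.0% and 81.5% at R2 = 0, 82.2% and 84.8% at R2 = 0.10, and 83.4% and 88.0% at R2 = 0.20. This agrees with the formula. It also shows the price when the strata carry no information: about half a point.

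**Simulation, logistic GEE.** The settings were 40 homes of 120 residents, ICC 0.10 and four equal strata. The article does not state the type of standard error, so an uncorrected sandwich with a z-test is an assumption.
- Strata omitted: type I error about 4.9% at R2 = 0.10 and 4.0% at R2 = 0.20.
- Strata included: about 7 to 7.5%.
- Strata included, with a small-sample correction: about 5%, with a power gain of about 2 to 5 points.

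**The case against.** **The list may not be closed.** The four covariates are introduced as resident characteristics, to deal with resident-level imbalance. Home-level terms are not excluded, and a full analysis plan could add them. This stands in part: a reader might infer that the trial will definitely be analysed as if unstratified, and the article does not say so. But it does name its covariates, and the stratification factors are not among them. Followed as written, the model omits them.

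**The size is assumed.** Profit status is linked to quality of care, not to vitamin D prescribing, and nothing is claimed for home size. This stands. The strata might explain nothing, and then nothing is lost.

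**The test need not be markedly conservative.** From the normal approximation a reader might infer an actual type I error of 4.0% at R2 = 0.10 and 3.0% at R2 = 0.20. Those figures treat the variance as known. With about 40 clusters, the downward bias of an uncorrected sandwich variance partly or wholly offsets the effect of omitting strata, and adding stratum terms without a correction pushes the error above 5%. This also stands. It limits the claim and changes the fix.

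**The trial is a pilot that emphasises feasibility.** That lowers the priority, but prescribing at 6 and 12 months is still a primary clinical outcome with a formal test.

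**Conclusion.** The point holds as a loss of precision. If size and profit status are prognostic, the model as written overstates the standard error by about 5 to 11% and gives up about 2 to 5 points of power against a stratum-adjusted model. This assumes R2 between 0.10 and 0.20 and the plan's own inputs; at R2 = 0 the loss is zero.

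A reader might infer that the trial is underpowered for this reason. It is not. On the same formula, power without strata is 81.4 to 82.7% at these R2 values, against 80.2% with no stratum effect, so it does not fall below what the plan's calculation delivers. Nor does leaving out the strata bias the comparison or inflate false positives; its own effect is conservative. I rate this as a cheap improvement.

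**What to change.** State in the Quantitative analysis section that every between-arm GEE (vitamin D, calcium, osteoporosis medication, falls, fractures) includes the home-size stratum used at randomisation and profit/non-profit status as fixed home-level terms. State in the same place that a small-sample-corrected sandwich variance with a t reference distribution is used. The two changes belong together, because stratum terms with an uncorrected z-test risk a type I error of about 7% with some 40 homes.

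The cost is a sentence or two and about 2 to 3 degrees of freedom. Power falls negligibly if the strata are not prognostic (81.5% against 82.0% in simulation). Both variables are already collected. The Data monitoring section defers formal comparison of the arms to the end of the study, so the change can be fixed before any comparison is made.
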